### Sample size estimation

Back pain and lower extremity injuries make up 44 % of all injuries for which soldiers seek care. Patients with back pain are seen on a daily basis in this healthcare system. Assuming at least 85 % of the patients complete the OSW at 12 weeks, enrollment of 110 subjects per group (total sample size 220 subjects) will provide at least 84 % power to detect a difference of seven points change in OSW at 12 weeks, assuming a standard deviation in the change in OSW of 16 points (treatment effect = 43.8 % of one standard deviation). The MCID for the OSW has been estimated at 6 points [19]. Previous work with patients with acute LBP indicate that these estimates of anticipated effect size and standard deviation are realistic, [44–46] and would be consistent with detecting an effect that is at least slightly in excess of the threshold for seeing significant change.

The natural history of recovery from back pain and our experience in prior studies suggest that differences tend to become less pronounced at 1 year than at 12 weeks. We believe 12 weeks is the appropriate time frame for the primary endpoint because it reflects the potential impact of treatment, and clinically, if patients are not experiencing improvement at this time point, they seek additional treatments. Thus, we are using this endpoint for the purposes of our power analysis rather than 1 year. The 4-week assessment will allow us to evaluate immediate post-treatment changes, and the 1-year assessment permits us to evaluate the potential long-term effects.

### Inclusion criteria

The inclusion criteria are as follows:Military personnel on active duty and eligible for healthcare at a military treatment facility;A primary complaint of low back pain defined as symptoms of pain and/or numbness between the 12^th^ rib and buttocks with or without symptoms into the leg(s), which, in the opinion of the provider, are originating from tissues of the lumbar region;Duration of current episode of low back pain ≤ 90 days;Age 18 to 60 years (or emancipated minors on active duty); andAvailable for the following 4 weeks to complete a regimen of treatment.

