Physical therapy is a treatment option for low back pain. Although utilization of physical therapy is relatively low, 7 to 16 % of those that seek care do so for low back pain, [8] and this utilization is slowly increasing [9, 10]. Despite the increasing utilization of physical therapy and associated costs, there is surprisingly little information on the effectiveness of physical therapy as an early management strategy for patients with low back pain. Recent evidence suggests that the timing of physical therapy may be one of the more important variables related to prognosis because it is associated with improved healthcare costs downstream and decreased future healthcare utilization. Two recent studies found that early physical therapy (<14 days) was associated with significantly less healthcare utilization and costs for the 18- to 24-month period past the episode of back pain [11, 12]. A separate study compared an initial management strategy of either advanced imaging or physical therapy for low back pain and found that choosing advanced imaging over physical therapy as the initial strategy resulted in significantly greater overall 1-year healthcare costs related to back pain (average of $4,793 more per person) [13]. This means that initial care decisions made by healthcare providers about low back pain, such as early referral to physical therapy, can have a substantial impact on cost and long-term outcomes. The timing of interventions, such as physical therapy, is an area that needs further inquiry, and has the potential to influence referral recommendations and treatment approaches for low back pain. While the value of early physical therapy for low back pain has been shown in cohort studies, it has not been evaluated prospectively in a clinical trial.

The purpose of this study is to assess the impact of early physical therapy in patients seeking care for low back pain. We will assess outcomes and related downstream costs for patients seen in primary care that either are referred for physical therapy immediately or are managed via usual care pathways.

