### Randomization

Randomization will be conducted using a blocked randomization list (block size 2 or 4) generated prior to the study. Randomization assignments will be sealed in opaque envelopes prior to beginning the study. Opening the randomization envelope will occur after completion of the baseline examination and the advice and education intervention, to avoid bias in the delivery of this aspect of the intervention. Patients in both groups will be instructed to follow-up with their primary care provider as needed. Patients in the PT group will be scheduled to begin physical therapy within 3 days.

We will record reasons for a subject dropping out of the study during any stage of the trial, and we will record all reasons for nonparticipation in the study to enable our ability to calculate an overall participation rate. The proposed flow of subjects through the study is depicted in Fig. 1.

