#### Physical Therapy (PT) treatment group

Patients in the PT group will receive the same initial management described above, and will then be referred to physical therapy within 48 hours. A maximum delay of 2 days should be inconsequential as typical recovery for back pain is 6 weeks, with a plateau at around 12 weeks [16]. The physical therapy treatment will be determined using a treatment-based classification approach, which has acceptable reliability [17]. This approach attempts to match a patient with an appropriate treatment based on their clinical presentation and relevant impairments. The three primary initial treatment approaches will use manual therapy (Additional file 2: Appendix 2), core strengthening (Additional file 2: Appendix 3), or an extension-oriented treatment approach (Additional file 2: Appendix 4). Typical of clinical practice within participating physical therapy clinics, the treating physical therapist will be allowed to modify the initial treatment strategy after 2 weeks of treatment if the patient demonstrates either substantial clinical improvement or worsening of symptoms. Substantial clinical improvement or worsening will be based on a repeat administration of the Oswestry Disability Index and patient self-report. Substantial improvement will be defined first by patient report and then verified objectively by administration of an Oswestry with improvement (that is, decrease in pain) of 50 % or more. Worsening will be identified first by patient report, and then defined as any deterioration (that is, increase) on a repeat Oswestry score. If either substantial improvement or deterioration is observed, the treating physical therapist may modify the initial treatment strategy. In other words, patients will also be progressed through the treatment program based on the clinical judgment of the treating physical therapist. Although they will start in one treatment group, they can progress to treatment in another group based on the directions of the physical therapist. Using the example above, if a patient has back pain with radicular leg symptoms that are successfully treated with the extension-oriented treatment approach after only five sessions and shows a subsequent improvement of 50 % on the Oswestry Disability Index, then the physical therapist may decide that the patient would benefit from core stabilization exercises and transition to this approach for the last three sessions, if impairments remain. All aspects of treatment provided to the PT group are part of the standard of care.

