### Physical examination

A clinician will conduct a physical examination composed of the examination variables required to identify the patient’s treatment-based cluster. These variables include questions related to the distribution and duration of the patient’s symptoms, neural tension tests, measures of spinal range of motion including the effects of motion on the patient’s symptoms, assessment of spinal mobility and tests of trunk muscle function.

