### Data analysis

The data analysis for hypothesis number 1 will use separate analyses of covariance (ANCOVA) to compare the mean change in the primary (OSW) and secondary (NPRS, FABQ, PCS and GRC) outcomes from baseline to each follow-up assessment between groups while controlling for the baseline level of the outcome being analyzed to account for regression to the mean. We will assess the influence of baseline psychosocial measures (PCS and FABQ) on outcomes in both groups by introducing the scores as covariates into the ANCOVA in order to address hypothesis #3. For hypothesis #2, we will use chi-square tests and calculate odds ratios with confidence intervals for the specific healthcare utilization frequently sought by patients with LBP (MRI, injections, work loss as measured by the DA3329 limited duty profile).

We will make every effort to achieve complete data collection. For data that are missing, we will use multiple imputation (MI). Under the MI approach, baseline and follow-up factors beyond the variable being analyzed can be incorporated into the imputation model to account for dependence of the missing data mechanism on other measured factors, such as predictors of patient characteristics and prior scores. We will apply the method of data augmentation using Markov Chain Monte Carlo (MCMC) to generate imputed values. Four steps are involved: a) preparing the dataset for MI, which includes identifying all outcome variables likely to be involved in later planned or unplanned analyses, as well as likely predictors of missingness itself, evaluating distributions for normality and outliers and taking appropriate transformations to normality as needed; b) carrying out the MI, where variance and covariance estimates based on observed data are used to iteratively estimate maximum likelihood values for all participants, with multiple replacement values for each missing data point then being drawn randomly from the posterior distribution and perturbed with error; c) carrying out analyses identically on all versions of the imputed data; and d) combining tests and parameter estimates and adjusting for between-imputation variance to yield the final statistical results.

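### Symptom duration at entry can range up to 90 days and is recorded at baseline, but the OSW ANCOVA does not adjust for it

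*Protocol article*

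**What the plan says.** The Inclusion criteria set the limit as "Duration of current episode of low back pain ≤ 90 days". The section on the Physical Therapy (PT) treatment group, arguing that a two-day wait does not matter, states that "typical recovery for back pain is 6 weeks, with a plateau at around 12 weeks". The Study design section describes the population as having recent onset.

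Under Physical examination, the baseline variables include "questions related to the distribution and duration of the patient’s symptoms". They are collected there to assign the treatment-based classification.

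The Data analysis section compares mean change in OSW, and in the secondary outcomes, at each follow-up by ANCOVA "while controlling for the baseline level of the outcome being analyzed to account for regression to the mean". The pain catastrophizing and fear-avoidance scores enter as further covariates for hypothesis 3. Symptom duration is not named. The Randomization section describes a blocked list with block size 2 or 4 and mentions no stratification by duration.

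On the meaning of early, the Background says patients "either are referred for physical therapy immediately or are managed via usual care pathways", and the Randomization section adds: "Patients in the PT group will be scheduled to begin physical therapy within 3 days".

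**The concern.** On the article's own account of natural history, a patient a few days into an episode and a patient near day 90 should differ in how much they will improve over the next 12 weeks whatever the treatment. That makes duration at entry a plausible predictor of the primary outcome. It is collected, and the plan names its covariates, but duration is not among them.

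Two modest things are at stake. Outcome variation that duration could explain stays in the residual, so the confidence interval is wider than it need be. And because no duration stratum is mentioned, the arms may differ in duration by chance, with nothing in the described model to adjust for it.

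**Working it through.** **Inputs from the article.** Entry limit 90 days (Inclusion criteria). Typical recovery 6 weeks = 42 days and plateau about 12 weeks = 84 days (PT treatment group). Difference 7 OSW points at 12 weeks, SD of change 16, 110 per arm, 85 % completion, power at least 84 % (Sample size estimation). The significance level is not stated there; two-sided 0.05 is assumed.

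**1. Spread of patients over the recovery course.**
- 90 / 7 = 12.9 weeks, so the limit lies just beyond the 12-week plateau.
- Days 85 to 90 lie past the plateau: 6 / 90 = 6.7 % of the entry window.
- Days 43 to 90 lie past the 6-week typical recovery: 48 / 90 = 53 % of the window.
- These are shares of days, not of patients. The article gives no distribution of duration.
- The 12-week endpoint falls 12 weeks after onset for a patient entering at onset. For one entering at day 90 it falls (90 + 84) / 7 = 24.9 weeks after onset.

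**2. Reproducing the stated power.**
- Completers per arm: 110 × 0.85 = 93.5.
- SE = 16 × √(2 / 93.5) = 2.34.
- Power = Φ(7 / 2.34 − 1.96) = 84.9 %. A noncentral t calculation with 93 per arm gives 84.3 %.
- Both agree with the stated figure, so the sample size is not in error.

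**3. What the covariate could add.** Take 16 as the residual SD before duration enters, and let duration explain a share R² of the residual variance. The SD becomes 16 × √(1 − R²). The values of R² are assumptions.

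| R² | Residual SD | Power for 7 points |
|---|---|---|
| 0 | 16.00 | 84.9 % |
| 2 % | 15.84 | 85.6 % |
| 5 % | 15.59 | 86.6 % |
| 10 % | 15.18 | 88.4 % |

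The cost if duration explains nothing is one residual degree of freedom. With 2 × 93.5 = 187 completers and three parameters (two arm means and the baseline slope), that is 184 falling to 183.

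**4. What a treatment-by-duration analysis could show.** Suppose the effect is 7 points in shorter-duration patients and 0 in a longer-duration share f (assumed). The SE of the difference in effects is 16 × √(2 / (93.5 f) + 2 / (93.5 (1 − f))).
- f = 20 %: SE = 5.85, power Φ(7 / 5.85 − 1.96) = 22 %.
- f = 50 %: SE = 4.68, power Φ(7 / 4.68 − 1.96) = 32 %.

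Even this extreme contrast would usually be missed.

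**The case against.** The strongest reply is that nothing is contradicted. The trial studies timing of access to a physical therapist from primary care, and patients who have had care for this episode in the last 3 months are excluded. A patient first presenting at day 85 who starts therapy within days is early in the sense that the trial uses. The Background does report that "Two recent studies found that early physical therapy (<14 days) was associated with significantly less healthcare utilization", but it does not say from what point the 14 days run, so it cannot show that onset was meant. This reply stands.

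A reader might go further and infer that already-plateaued patients are being pooled as early, so that the treatment effect is diluted and a null result could not be read. The article does not support that:
- Only days 85 to 90 lie past the plateau, and patients with an OSW below 20 % are excluded.
- The article nowhere says that therapy works less well later in the episode.
- Dilution can be computed only from assumed inputs. For example, if 20 % of patients had no effect, the average would be 7 × 0.80 = 5.6 points and power 66.8 %. Neither the 20 % nor the zero effect has a source in the article, and a duration covariate would not restore a diluted average.

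The planning values and the MCID come from acute low back pain, but acute is not defined, so a mismatch with the 90-day limit cannot be shown.

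It is also fair that baseline-adjusted ANCOVA is a sound primary model, that the pragmatic aim is the average effect over presenting patients, and that a duration subgroup may sit in an analysis plan not shown. But the article does name its covariates, so asking for one more addresses a stated choice. The article does not list duration as a predictor of OSW change; its prognostic value is inferred from the recovery course that the article cites.

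**Conclusion.** The point holds as a low-cost improvement and not as an error. The described OSW model leaves out a baseline variable that is already collected and, on the article's own recovery course, probably prognostic. The comparison remains unbiased by virtue of randomization, and the 84 % power claim is correct under the stated inputs.

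The size is small: from 84.9 % to between 85.6 % and 88.4 % power, plus adjustment for chance imbalance in duration. This rests on a two-sided 5 % level, an SD of 16 before duration enters, and duration explaining 2 to 10 % of the residual variance. The last is an assumption that the article can neither confirm nor exclude. An interaction analysis, at about 22 to 32 % power under a generous contrast, is too weak to carry any conclusion.

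**What to change.** - Add baseline symptom duration, in days and as a continuous variable, as a prespecified covariate in the OSW ANCOVA at 4 weeks, 12 weeks and 1 year. Fix this before unblinding.
- Include duration in the multiple imputation model. The Data analysis section already allows further baseline factors there.
- Confirm that the baseline form records duration in days, since the article does not give the format.
- If a treatment-by-duration estimate is wanted, report it with its confidence interval and label it exploratory.
- In the conclusions, describe early as early after first consultation, not after onset.

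The cost is one degree of freedom in each model and one more if the exploratory interaction is fitted. Eligibility, recruitment and sample size do not change.

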### Exclusion Criteria

Exclusion criteria are as follows:Oswestry Disability Index <20 % (prevent a ceiling effect).History of receiving any medical care for this episode of low back pain within the last 3 months.Prior surgery to the thoraco-lumbar spine or pelvis.This episode of back pain is due to a traumatic fracture.Pending a medical or physical evaluation board or discharge process, pending any litigation related to the condition, or planning on getting out of the military within the next 9 months.Any “red flags” that would indicate a potentially serious condition or other significant disease process. These could include but not limited to cauda equina syndrome, large or rapidly progressing neurological deficit, fracture, cancer, ankylosing spondylitis, or other systemic disease.Current episode occurred because of a motor vehicle accident.Currently pregnant (or history of pregnancy in the previous 6 months).

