#### Hypothesis

The following hypotheses will be tested:Early intervention strategies utilizing physical therapy will result in greater improvements in function and disability in the long-term compared to a stepped usual care approach.Early intervention strategies utilizing physical therapy will result in decreased use of other medical resources (medications, imaging, additional healthcare) in the long-term (1 year) compared to a stepped usual care approach.Baseline psychosocial factors will be associated with changes in clinical outcomes within each treatment group.

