### Healthcare utilization

Finally, healthcare utilization data will be collected from the Military Health System Data Repository (MDR) database and will be confirmed via electronic medical record review. Healthcare utilization data will be used to determine any subsequent medical utilization related to low back pain and the economic impact of those injuries. These data will also allow a comparison of costs between the two treatment approaches used in this study.

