It is feasible for patients with a new episode of LBP to receive physical therapy as part of an early management strategy [8]. However, physical therapy also contributes substantially to the healthcare costs associated with managing LBP [48, 49]. Along with the increasing utilization of physical therapy for LBP, are the corresponding costs that are also increasing [9, 10]. In the last 10 years, physical therapists in the US Army are now providing medical care further up on the front lines with the infantry soldiers as an organic asset to their unit. These therapists are in a prime position to facilitate early access to physical therapy interventions and have done so successfully in a combat-deployed setting [50, 51]. Considering that about 60 % of patients report recurrent symptoms, and 20 % report persistent disabling symptoms following an initial LBP episode [52, 53], research examining the most effective initial management strategies and the potential role of physical therapy is clearly needed. Suboptimal effectiveness of primary care management for patients with an acute episode of LBP can also lead to use of increasingly invasive and costly interventions, including injections, narcotic pain medications and surgical procedures [54–56]. In addition to the significant fourfold increase in prescription pain medication use in soldiers, other significant military healthcare costs are associated with the diagnostic management of these soldiers. In the current combat environment, advanced diagnostic imaging is not readily available [51]. Tests that would routinely be ordered in regular hospitals/clinics, when ordered in a combat setting, often require an evacuation out of the theater, incurring significant additional evacuation costs and time loss from duty. Especially for low back pain, many of these tests do not offer a valid prognosis or provide guidance for treatment and likely lead to an increase in overall medical costs [20, 57]. Reducing trends toward increased utilization and costs associated with prolonged episodes of LBP will require more effective early management strategies [58]. In a combat deployed setting, effective management strategies have the potential to decrease significantly the number of unnecessary evacuations out of the combat theater. The initial primary care encounter may therefore provide the best window of opportunity to improve outcomes and reduce costs related to low back pain.

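### The utilisation comparison uses chi-square tests that cannot adjust for earlier back-pain care, although patients recently treated for a previous episode can enter

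*Protocol article*

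**What the plan says.** The Exclusion Criteria of the protocol article remove patients with a "History of receiving any medical care for this episode of low back pain within the last 3 months". The Inclusion criteria require "Duration of current episode of low back pain ≤ 90 days". The only exclusion that expressly reaches back-related treatment before the current episode is "Prior surgery to the thoraco-lumbar spine or pelvis". The article gives no symptom-free or care-free interval that would separate a new episode from a flare of an old one. Its Discussion notes that "about 60 % of patients report recurrent symptoms" after an initial episode.

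Under Healthcare utilization, the MDR, confirmed by record review, supplies "any subsequent medical utilization related to low back pain and the economic impact of those injuries", and a cost comparison between the arms is intended. For hypothesis 2, the Data analysis section says "we will use chi-square tests and calculate odds ratios with confidence intervals for the specific healthcare utilization", naming MRI, injections and work loss. For hypothesis 1, the same section specifies ANCOVA controlling for the baseline level of each outcome. The Randomization section describes blocks of 2 or 4 and names no stratification by prior care.

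**The concern.** The exclusion reads like a 3-month washout of care, but it is tied to an episode that can be no older than about 3 months. It therefore removes only patients already treated in the current episode. Someone who had physical therapy, an MRI or an injection a few weeks ago for what is judged a previous episode passes it.

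Earlier back-pain care plausibly predicts later back-pain care. Some follow-up events may even be care already under way at enrolment. The utilisation analysis has no means of taking this into account. Hypothesis 1 uses a baseline measure to sharpen the comparison; hypothesis 2 does not, although its natural baseline should sit in the database already being queried. At stake are the precision of the utilisation comparison and how far a chance excess of prior users in one arm colours it.

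**Working it through.** **1. The eligibility wording.** Care for an episode cannot precede its onset. Onset is at most 90 days before entry, which is about 3 months. So the set of patients with care for this episode within 3 months is the same as the set with any care for this episode, and the time limit removes nobody further. Care for an earlier episode, however recent, meets no exclusion in the list unless it was thoraco-lumbar or pelvic surgery.

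**2. The plan's own figure.** The only power statement concerns the Oswestry score at 12 weeks: 7 points, SD 16, 110 per arm, 85 % completion, at least 84 % power. With 110 × 0.85 = 93.5 per arm, standardised effect 7/16 = 0.4375 and two-sided alpha 0.05 (assumed; the article states none), power is 84.9 % by the normal approximation and 84.5 % by the noncentral t. The figure reproduces and does not depend on this point. The article gives no power figure for utilisation.

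**3. Chance imbalance in prior users.** Let q be the share of entrants with recent earlier care. The article does not give it, so 10 to 60 % is assumed. The between-arm difference in that share has mean zero and SD √(2q(1−q)/110).
- q = 10 %: √(0.18/110) = 0.040; 95 % range ±1.96 × 0.040 ≈ ±8 percentage points.
- q = 60 %: √(0.48/110) = 0.066; 95 % range ±1.96 × 0.066 ≈ ±13 percentage points.

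**4. Consequence for the test.** Simulation with 110 per arm and 40,000 replicates per scenario. Assumed inputs: event risk 20 % without prior care, multiplied by 1.5, 2 or 3 for prior users, and a true conditional odds ratio of 0.5. The unadjusted chi-square is compared with a Mantel-Haenszel test stratified on prior care, as a stand-in for covariate adjustment.

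With no treatment effect, the chi-square rejects in 4.8 to 5.1 % of replicates across all nine scenarios. Power with the effect present:

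| q | Risk ratio | Chi-square, % | Stratified, % | Difference, points |
|---|---|---|---|---|
| 10 % | 1.5 | 46.01 | 45.74 | −0.27 |
| 10 % | 2 | 46.45 | 46.64 | +0.19 |
| 10 % | 3 | 44.92 | 47.76 | +2.84 |
| 30 % | 1.5 | 48.56 | 48.52 | −0.04 |
| 30 % | 2 | 50.64 | 51.88 | +1.24 |
| 30 % | 3 | 48.67 | 54.42 | +5.75 |
| 60 % | 1.5 | 52.40 | 52.85 | +0.45 |
| 60 % | 2 | 56.87 | 58.53 | +1.66 |
| 60 % | 3 | 57.11 | 63.05 | +5.94 |

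The simulation error of each power estimate is about √(0.5 × 0.5/40,000) = 0.25 points, so the small negative differences are effectively zero. The gain depends mainly on how strongly prior care predicts later events. It is negligible at a risk ratio of 1.5 and approaches 6 points at 3.

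**The case against.** The case against has real force.

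- **Eligibility.** A redundant time limit is not a failed washout. The criterion still removes patients already treated in this episode, which suits a question about timing of physical therapy after a recent onset. A pragmatic trial may well want recurrent cases. A reader might infer that a washout across episodes was intended and that the exclusion must be reworded. Nothing in the article shows that intention, and changing entry criteria during recruitment has its own cost. This part of the objection stands.
- **Validity.** A reader might infer bias or a raised false-positive rate. Allocation is randomised, so prior use is balanced in expectation, the simulated error rate is nominal, and the planned confidence intervals already carry the chance variation. This stands too.
- **Scale.** It is tempting to apply the 60 % recurrence figure to 220 entrants (132), and then the article's 7 to 16 % physical therapy use (9 to 21). The first figure describes recurrence after an initial episode and the second has no time limit, so neither measures recent prior care. Likewise, 220/(1−R²) with an assumed R² of 10 to 30 % gives 244 to 314 equivalent patients, but that is a linear-model formula. It does not carry over to odds ratios for binary events.
- **A condensed article.** How an episode is defined, and further covariates, may sit in the full protocol or SAP. That is fair for the definition. It does not fully answer the analysis point: the article names a method for hypothesis 2 that takes no covariate, beside one for hypothesis 1 that does.

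**Conclusion.** The point holds as a modest and cheap improvement to a stated method. Certain from the text: the 3-month window adds nothing to the current-episode limit, patients recently treated for an earlier episode can enter, and the named utilisation test cannot adjust for prior use.

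The consequence is lost precision and unadjusted chance imbalance, not bias. For binary endpoints the loss is roughly 0 to 6 points of power, conditional on the assumed prior-use share, event risk, risk ratio and treatment effect, none of which the article gives. For cost, the gain depends on how strongly prior use predicts later cost, which is also not given. That the MDR holds usable pre-enrolment records is a reasonable expectation, but the article does not say so. The primary Oswestry analysis is unaffected.

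**What to change.** Extract each participant's back-pain-related utilisation for the 12 months before enrolment from the MDR. Include it as a prespecified covariate in the hypothesis 2 analyses: logistic regression for MRI, injection and work-loss events, and an adjusted model for cost. Fix the form of the covariate (for example any prior use, or prior cost) before the arms are compared. Keep the chi-square tests as supportive analyses.

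The cost is a longer look-back in an extraction already planned and one extra covariate. The adjusted odds ratio is conditional rather than marginal, so the plan should say which is reported, or standardise to recover the marginal one.

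The sponsor may also state what the 3-month window was meant to cover. Eligibility need not change.
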